## Précis

A vaccine to interrupt malaria transmission would be a valuable tool for local elimination or eradication of this disease. Pfs25, a surface antigen of ookinetes in the mosquito stage of *P. falciparum*, is a lead candidate for a malaria transmission blocking vaccine. Recombinant Pfs25 has been conjugated to *Pseudomonas aeruginosa* ExoProtein A (EPA), and adjuvanted with Alhydrogel®. This open label, dose escalating Phase 1 study in malaria naïve adults, conducted at Johns Hopkins Bloomberg School of Public Health Center for Immunization Research (CIR) in Baltimore, Maryland, will determine initial safety and immunogenicity of the vaccine given on a 2 dose and 3 dose schedule. Thirty (30) volunteers will be enrolled, with 5 receiving the lowest dose (8 µg of conjugated Pfs25), 5 receiving the middle dose (16 µg of conjugated Pfs25), and 20 receiving the high dose (47 µg of conjugated Pfs25). The low dose groups will receive 2 doses of vaccine and the high dose group will receive 4 doses of vaccine, on a 0, 2 month (low dose) or 0, 2, 4 and 10 month (high dose) vaccination schedule. In addition, extraordinary responders to the low dose of vaccine (as measured by antibody level) will be offered a booster dose at 10 months. Volunteers will be followed for 12 months following the last vaccination. Safety outcomes will be local and systemic adverse events (AEs). Immunogenicity outcomes will be antibody responses as measured by ELISA, transmission blocking in a standard membrane feeding assay, and B and T cell responses.

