## **3.2 Study Endpoints**

### **3.2.1 Primary Endpoints**

The incidence and severity of systemic and local AEs

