## **9 Safety and Adverse Event Reporting**

### **9.1 Definitions**

#### **Adverse Events**

An adverse event (AE) includes any untoward or unfavorable medical occurrence in a human subject, including any abnormal sign (e.g. abnormal physical exam or laboratory finding), symptom, or disease, temporally associated with the subject's participation in the research, whether or not considered related to the research. This includes an exacerbation of pre-existing conditions and intercurrent illnesses. All AEs will be graded for severity and assessed for

relationship to the investigational vaccine as described below.

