## 9.3 Assessment of Adverse Events

Assessment of safety will include clinical observation and monitoring of hematological, chemical, and immunologic parameters. Subjects will be closely monitored for 30 minutes following each immunization. Additionally, subjects will return to the clinic on Days 3, 7, 14, and 28 following each vaccination for clinical assessments, and periodically thereafter until completion. All AEs will be recorded through Day 28 after each vaccination. Injection site reactions will be assessed until day 14 or until resolved. After that period only SAEs, UPs, and NOCIs ([Section 9.1](#)) will be recorded.

All AEs will be graded for severity and assessed for relationship to the study product. Reactions

will be graded as described in this protocol. A study clinician will be available 24 hours a day during the study period. Should a subject call a study clinician to report an AE, it will be fully documented in the subject's study chart, and discussed with the PI.

All local and systemic reactions will be captured on the appropriate source documents and CRIMSON Data System. Those assessed as serious will be further reported on the Sponsor's SAE/UP report form. AEs judged to be possibly, probably, or definitely related to the study product will be followed to adequate resolution. All concomitant medications will be collected through day 28 after each vaccination; new chronic medications will be collected for the remainder of the study.

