**Table 3 Solicited Adverse Events**

| Systemic adverse events | Laboratory adverse events | Local reactogenicity |
|-------------------------|---------------------------|----------------------|
| Fever                   | Hemoglobin                | Injection pain       |
| Headache                | WBC                       | Injection erythema   |
| Nausea                  | ANC                       | Injection swelling   |
| Malaise                 | ALT                       | Injection induration |
| Myalgia                 | Platelet count            | Injection pruritus   |
| Arthralgia              | Creatinine                |                      |
| Urticaria               |                           |                      |

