### 11.2 Primary Objective

The primary objective of this study is to assess safety and reactogenicity of Pfs25-EPA/Alhydrogel® in malaria-naïve US adults.

- a. The frequency of systemic and local AEs will be summarized.
- b. A line listing of each clinical and laboratory AE classified as local, solicited, or other will be displayed in tables stratified by vaccine allocation.
- c. AEs will be summarized by severity and relationship to vaccine (according to [Table 4](#)).
- d. The proportion of subjects with at least 1 AE will be compared by vaccine schedule and/or dose group, and tests performed to assess whether these groups differ with respect to these proportions. To see if there is a difference in AEs between the initial vaccination and the subsequent vaccinations, a Wilcoxon signed rank test will be performed, where the response for each subject is the difference between the numbers of AEs in the 2 weeks following each vaccination.
- e. SAEs occurring within the study period will be listed by relationship to vaccine.

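### The only between-group AE test counts any AE over no fixed window, while the primary endpoint is systemic and local AEs and the groups have 2 versus 4 planned doses

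*Protocol*

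**What the plan says.** - **Endpoint.** Protocol section 3.2.1 gives the primary endpoint as "The incidence and severity of systemic and local AEs".
- **Test.** Section 11.2, item d: "The proportion of subjects with at least 1 AE will be compared by vaccine schedule and/or dose group", followed by tests of whether the groups differ. No AE class, grade, relationship or window is given for this proportion. The second part of item d, a signed rank test within subjects between vaccinations, does have a 2-week window.
- **What counts as an AE.** Section 9.1 defines an AE as "including any abnormal sign (e.g. abnormal physical exam or laboratory finding") and says that it counts "whether or not considered related to the research".
- **Classes.** Table 3 sorts solicited events into three columns: "Systemic adverse events | Laboratory adverse events | Local reactogenicity". Item b of 11.2 lists events "classified as local, solicited, or other".
- **Collection.** Section 9.3: "All AEs will be recorded through Day 28 after each vaccination".
- **Exposure.** Précis: "The low dose groups will receive 2 doses of vaccine and the high dose group will receive 4 doses of vaccine". Table 1 adds an optional month-10 dose for Groups 1a and 1b.
- **Other summaries.** Items a and c of 11.2 summarize the frequency of systemic and local AEs, and AEs by severity and relationship. Section 11.1 describes the study as exploratory and aimed at estimation.

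**The concern.** Items a and d sit in the same section but use different variables. Item a follows the endpoint. Item d, the only comparison of AEs between groups, uses a wider count and leaves out severity, which the endpoint includes.

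Two things follow. First, events that do not depend on dose enter the count in every group. Blood counts, ALT, creatinine and urine dipstick are repeated after each dose, and Appendix C grades even trace urine protein as Grade 1, so such events are plausible. They push all the proportions up and shrink the gap between them. Second, with no stated window, a subject in Group 2 has about twice as many 28-day recording periods as a subject in Group 1, and so more chances of at least one AE even if dose has no effect.

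The errors run in opposite directions. A non-significant result would say little about reactogenicity, and a significant one might reflect only the number of doses.

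**Working it through.** **Inputs from the protocol.** Group sizes 5, 5 and 20; planned doses 2, 2 and 4; AEs recorded for 28 days after each dose.

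**Assumptions, because the protocol gives no figure.** A two-sided Fisher exact test at 0.05; Groups 1a and 1b pooled (n=10) against Group 2 (n=20); the reaction rates and background rates below; background independent of reactions and equal in both groups.

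**The protocol's own safety figures.** Section 11.4 gives at least 0.80 probability of seeing one or more serious or severe AEs. With 1−(1−p)^n: 1−(1−0.275)^5 = 0.7997 and 1−(1−0.052)^30 = 0.7985. Both reproduce. They concern detection of severe events; no power or expected rate is stated for the item d comparison.

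**Dilution.** If r is the reaction rate and B the background rate, the proportion with any AE is 1−(1−r)(1−B). With r = 20% (Group 1) and 70% (Group 2), the gap is (0.70−0.20)(1−B):

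| B | Group 1 | Group 2 | Gap (points) | Fisher power |
|---|---|---|---|---|
| 0 | 20% | 70% | 50 | 66% |
| 30% | 44% | 79% | 35 | 43% |
| 50% | 60% | 85% | 25 | 28% |
| 70% | 76% | 91% | 15 | 15% |
| 80% | 84% | 94% | 10 | 9% |
| 90% | 92% | 97% | 5 | 2% |

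Example at B = 50%: 1−0.80×0.50 = 60% and 1−0.30×0.50 = 85%.

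Other assumed reaction rates show the same pattern at B = 0, 30%, 50%, 70% and 90%:
- 30% vs 80%: 73%, 48%, 32%, 16%, 2%.
- 40% vs 90%: 80%, 57%, 39%, 18%, 2%.
- 20% vs 60%: 45%, 26%, 18%, 10%, 2%.

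**Unequal windows, no dose effect.** With AE probability b per window, independent across windows, the proportion with any AE is 1−(1−b)^2 in Group 1 and 1−(1−b)^4 in Group 2:

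| b | Group 1 | Group 2 | Fisher rejects |
|---|---|---|---|
| 10% | 19% | 34% | 7.9% |
| 20% | 36% | 59% | 14.1% |
| 30% | 51% | 76% | 23.5% |
| 40% | 64% | 87% | 25.7% |
| 50% | 75% | 94% | 23.3% |
| 70% | 91% | 99% | 4.7% |

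Example at b = 30%: 1−0.7^2 = 0.51 and 1−0.7^4 = 0.76. This error arises only if item d is applied over the whole follow-up, a reading that the text permits and does not exclude.

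**The case against.** The strongest reply is that little depends on this test. Section 11.1 puts estimation first, and items a and c report systemic and local frequency, severity and relationship. A reader might infer from item d that the any-AE proportion will approach 100% and that a dose difference will be lost. The protocol does not support that: it gives no background rate, and the descriptive tables keep the information. This stands, and it limits the point to the test. But 11.1 also keeps formal tests as outlined, and item d is the between-group one for the primary objective.

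A reader might also infer that 3.2.1 excludes unsolicited or unrelated events. It does not: an unrelated systemic AE falls within its words. The clearest mismatches are laboratory AEs, which Table 3 sets apart, and the missing severity component. Even the first rests on Table 3, which sorts solicited events and does not define the endpoint. Restricting the test to solicited events is therefore a sharper measure of reactogenicity, not a literal match to 3.2.1, and some background remains, since an unrelated headache is still a solicited event.

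An any-AE count is a legitimate safety measure, and late and laboratory events matter here. Section 1.3 reports a leukemoid reaction 14 days after a second dose of an earlier Pfs25 formulation, and halting rule 4 counts laboratory abnormalities. That is a reason to keep those summaries, not to make them the test of reactogenicity by dose.

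Small groups limit power in any case: at zero background, 40% vs 70% gives 28% and 50% vs 80% gives 34%. True, but it is no reason to lose more. Finally, the overlapping labels in item b affect a listing only and change no estimate.

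**Conclusion.** The point holds in limited form. Item d tests a wider variable than the endpoint, omits severity and fixes no common window although planned exposure is 2 versus 4 doses. Under the assumed 20% vs 70%, a 30% background lowers power from 66% to 43%, and a 70% background to 15%. With no dose effect, unequal windows can raise the rejection rate to about a quarter. The direction of dilution follows from the definitions; its size rests on assumed reaction and background rates, on pooling Groups 1a and 1b, and on the Fisher test at 0.05. The consequence is a test that is hard to interpret, not a report without reactogenicity data. This is an inexpensive improvement and does not call the study's safety description into question.

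**What to change.** In section 11.2, item d, compare the proportion of subjects with at least one solicited local or systemic AE (Table 3, columns 1 and 3), by maximum grade. Use the same post-dose window in every group and the same dose number: after dose 1 and, separately, after dose 2, which all groups are scheduled to receive. The period covered by the symptom card (section 6.6) is a natural window.

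Keep the any-AE, laboratory and unsolicited AE proportions as descriptive summaries with 95% confidence intervals, by grade and relationship. If item b is edited at the same time, classes that do not overlap (solicited local, solicited systemic, laboratory, unsolicited) would make the listing clearer; that is layout only.

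Cost: wording and table shells, with no new data. Late, laboratory and unsolicited events are then described and not tested, so the descriptive tables must carry them. Power stays modest with 5, 5 and 20 subjects: under the assumed 20% vs 70% it is 66% for 10 vs 20.

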### 11.3 Secondary Objective

The secondary objective of this study is to determine the antibody response of the Pfs25 protein vaccines as measured by ELISA and transmission blocking assays as measured by SMFA, and the effect on antibody responses of a third (booster) dose at 4 months. An additional objective is the effect on antibody responses of a longer term booster (third or fourth dose) at 10 months (approximately 6 to 9 months after last dose).

Anti-Pfs25 antibody will be measured by ELISA on vaccination days, 2 weeks after each vaccination, and periodically until study completion. Antibody responses over time will be shown graphically with geometric mean antibodies and the associated confidence intervals based on the t-distribution applied to the log transformed responses. While Group 1 is included primarily for safety, we will still be able to examine a dose effect.

- Dose effect: Here we can compare the antibody responses at 2 weeks after the second

vaccination using all 3 Groups. We use a Jonkheere-Terpstra test (which is a generalization of the Wilcoxon Mann Whitney test for the case when there are three or more ordered groups), to test for the dose effect.

Graphs will display transmission blocking assays as a function of ELISA antibody levels.

### 11.3.1 Exploratory Objectives

- To determine T- and B-cell responses to vaccination.

Should the study be terminated early, the investigative team will discuss with the SMC the reason for termination and determine which study questions can be addressed in an unbiased manner with the available data. The available data will be analyzed and interpreted in light of early termination.

### 11.4 Sample Size and Power Calculations

The study is powered to provide sufficient safety data before dose escalation (between Groups 1a, 1b, and Group 2) and before proceeding to a Phase 1 study in a malaria-exposed population. Group 1 is sized for safety, as the higher dose is expected to be necessary for an adequate immune response. In Groups 1a and 1b, 5 subjects will receive 8 and 16 µg Pfs25-EPA/Alhydrogel®, respectively. Vaccination of 5 subjects gives a probability of at least 0.80 for detecting one or more serious or severe AEs that occurs with a probability of 0.275 or more per subject. For the study as a whole, vaccination of 30 subjects gives a probability of at least 0.80 for detecting one or more serious or severe AEs that occurs with a probability of 0.052 or more per subject.

To test for an antibody response by dose between the three dose groups, we use the Jonckheere-Terpstra (J-T) test which is a generalization of the Wilcoxon Mann Whitney (WMW) test from two groups to three or more ordered groups (e.g., low, middle and high dose groups). For the sample size calculations, we consider the simpler situation where the lower two dose groups are combined into one group and tested by WMW test. This simpler situation ignores differences in antibody response between the two lower dose groups; therefore the actual J-T test which does not ignore those differences should be at least as powerful as the simplifying situation. For the power calculation for the simplified situation we first estimate the standard deviation of the (log transformed) antibody response. To do this, we use data on the 5 subjects who received 2 doses of Pfs25/ISA51 vaccine in [Wu et al 2008]. From that data the standard deviation of the log transformed ELISA responses 2 weeks after the second vaccination was 0.33. After accounting for the fact that the standard deviation was estimated from only 5 observations [Fay et al 2007], a Z-test of the difference in means with 4 and 16 observations would have about 80% power to reject at the 2-sided 0.05 level if the geometric mean ELISA values was 4.5 fold higher in the larger dose group (the group with n=16). Because we use the WMW test instead of a Z-test, these results should hold with an increase in the sample size by 5% since the WMW test is about 95.5% as efficient as a Z-test in this situation [Lehmann 1999], i.e., the sample sizes of 10 (low and middle dose combined) and 20 (high dose) will have about 80% power to show a 3 fold difference between the lower two doses and the high dose. Thus, when we use the information

about differences between the low and middle dose groups (i.e., use the J-T test), we should have at least 80% power if there was a difference of 3 fold between the middle and high dose and possibly a larger difference between the low dose and high dose.

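### The planned Jonckheere-Terpstra test is not always at least as powerful as the pooled Wilcoxon test used for sizing: it is slightly weaker if the low and middle doses respond alike

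*Protocol*

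**What the plan says.** Protocol section 11.3 names the Jonckheere-Terpstra test across the three dose groups (5, 5 and 20 subjects) as the test of dose effect on antibody level two weeks after the second vaccination.

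Section 11.4 does not compute power for that test. It computes power for a simpler one, a Wilcoxon-Mann-Whitney (WMW) test with the two lower doses pooled, and concludes that "the sample sizes of 10 (low and middle dose combined) and 20 (high dose) will have about 80% power to show a 3 fold difference". It carries this over to J-T by argument: pooling ignores any low-middle difference, "therefore the actual J-T test which does not ignore those differences should be at least as powerful as the simplifying situation". It ends by saying that "we should have at least 80% power if there was a difference of 3 fold between the middle and high dose", adding that the gap between low and high may be larger still. The larger gap is offered only as a possibility, so equal low and middle responses fall within the statement.

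**The concern.** The argument treats the extra low-versus-middle information as free. It is not. J-T adds a 5-versus-5 comparison to the pooled statistic, and that comparison has its own sampling variance. When the two lower doses differ enough, the added signal outweighs the added noise. When they respond alike, only the noise is added and J-T must lose power relative to the pooled test.

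The equal-response case is plausible here. Sections 3.1 and 11.4 both expect the higher dose to be needed for an adequate immune response, so two similar, weak responses at 8 and 16 µg would be no surprise. At stake is the accuracy of the protocol's one power statement for a hypothesis test. It is worded as a minimum for a test whose power was not calculated.

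**Working it through.** **Inputs, all from section 11.4 unless marked**
- Group sizes 5, 5, 20; two-sided level 0.05; effect 3-fold.
- SD: "the standard deviation of the log transformed ELISA responses 2 weeks after the second vaccination was 0.33". The log base is not stated. Log10 is assumed, because it reproduces the protocol's figures; natural logs would give about 98.5% power for the 4-versus-16 case described as about 80%.
- SD uncertainty: "After accounting for the fact that the standard deviation was estimated from only 5 observations". The formula is not given. It is taken here as 4 degrees of freedom (assumption).
- Efficiency: "the WMW test is about 95.5% as efficient as a Z-test in this situation".
- Normal log responses with equal SD, no ties and no dropout (assumptions).

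**Step 1. Reproduce the protocol's figures.** Noncentrality = log10(fold) / (0.33 × √(1/n1 + 1/n2)). Expected power is the average of Φ(noncentrality × √(x/4) − 1.96) over x from a chi-square on 4 df.
- 4 versus 16 at 4.5-fold: 0.6532 / (0.33 × 0.5590) = 3.541, giving 80.6%. The protocol says about 80%.
- 10 versus 20 at 3-fold: 0.4771 / (0.33 × 0.3873) = 3.733. With efficiency 0.955 this gives 82.0%. Direct simulation of the WMW test, drawing the true SD as 0.33 × √(4/chi-square(4)), gives 79.9%. The protocol says about 80%.

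The stated figures for the simpler tests therefore stand.

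**Step 2. Compare the two statistics when low = middle.** J-T equals the pooled Mann-Whitney count plus the 5-versus-5 count. Under equal responses the added count has its null mean, so the shift away from the null is the same for both tests. The null variances differ:
- Pooled WMW: 10 × 20 × 31 / 12 = 516.67.
- J-T: [30² × 63 − (5² × 13 + 5² × 13 + 20² × 43)] / 72 = (56,700 − 17,850) / 72 = 539.58.
- Difference: 22.92 = 5 × 5 × 11 / 12, the variance of the low-versus-middle comparison.

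The J-T noncentrality is therefore √(516.67 / 539.58) = 0.9785 of the pooled one. A pooled power of exactly 80% becomes Φ(2.8016 × 0.9785 − 1.96) = 78.3%.

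**Step 3. Simulate at 5/5/20.** High is 3-fold above middle, with SD uncertainty as in step 1.

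| Middle/low ratio | Pooled WMW | J-T |
|---|---|---|
| 1.0 | 79.9% | 78.1% |
| 1.05 | 80.9% | 79.5% |
| 1.1 | 81.8% | 80.7% |
| 1.3 | 84.6% | 84.5% |
| 1.35 | 85.1% | 85.2% |
| 1.5 | 86.7% | 87.0% |
| 2.0 | 89.7% | 90.8% |

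At equality the difference is 1.9 points before rounding, with a simulation standard error of 0.02 points. J-T passes 80% by about a 1.1-fold low-middle difference and overtakes the pooled test at about 1.35-fold.

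**Step 4. Sensitivity of the equal-response case**
- Both tests randomized to exactly the 0.05 level: 80.0% pooled, 78.8% J-T.
- The protocol's own approximation, with efficiency 0.955 for WMW and 0.955 × 0.9575 = 0.9144 for J-T: 82.0% and 81.0%.
- SD taken as known at 0.33: 93.6% and 91.8%.

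The level of power depends on the modelling. The ordering does not: J-T is below the pooled test in every version.

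**The case against.** A reader might go further and infer that the 80% figure is simply false, or that the trial is underpowered. The documents do not support that.
- The shortfall at exact equality is about 2 points. Part of it is discreteness: the attained exact levels are 0.0465 for J-T and 0.0490 for WMW, and at a common level the gap shrinks to 1.2 points.
- By the protocol's own efficiency approximation J-T has 81.0%. That approximation runs about 2 points high for the pooled test at these sizes (82.0% against 79.9% simulated), so it is not decisive. It does show that the figure cannot be called plainly wrong.
- The shortfall is gone once doubling the dose from 8 to 16 µg raises the geometric mean by about 10%. The closing sentence of section 11.4 argues from low-middle differences being present; equality is its boundary case.
- The SD comes from five subjects given a different formulation. Treating it as known moves power by more than 10 points, which dwarfs the gap at issue.
- Section 11.1 calls the study exploratory, the antibody comparison is a secondary objective, and section 11.4 sizes Group 1 for safety. That section also gives two 0.80 detection probabilities for adverse events, so the dose-effect figure is not the protocol's only probability statement.

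All of this limits the consequence, and it stands. It does not rescue the ordering claim. That claim is a general statement used as a logical step, and it fails over a range of low-middle ratios from 1.0 to about 1.3, not at a single point.

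**Conclusion.** The claim that J-T is at least as powerful as the pooled Wilcoxon test is not true in general. With low and middle responding alike, J-T has about 78% power against about 80% at 3-fold, and it stays slightly behind until the middle response is about 1.35-fold above the low. The stated minimum of 80% is missed by about 2 points, and only for low-middle differences below about 1.1-fold; describing it as about 80% would be accurate.

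The direction of the result at equality follows from the null variances alone. The percentages rest on the log10 base, the 4-df treatment of SD uncertainty, normal log responses with a common SD, and complete data. The sample size is not called into question. Severity is minor.

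**What to change.** In section 11.4:
1. Delete the clause saying that J-T is at least as powerful as the simplified test.
2. Replace the minimum of 80% with the power of J-T itself, for example: about 78-80% at 3-fold if the low and middle doses respond alike, rising to about 87% if the middle-dose response is 1.5-fold above the low.
3. State the log base of the 0.33 SD and how its uncertainty was allowed for.

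The cost is two sentences and a slightly less favourable power statement. Enrolment, conduct and the choice of test do not change.
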